### Ethical Considerations

#### Institutional Review Board Approval

Two institutional review board (IRB) requests have been submitted to the University of California Irvine (UCI) institutional review board. The first IRB request (non–human subject research), approved in December 2023 (UCI IRB #3795), related to accessing publicly available data sets containing multimodal and sensory input data for modeling emotion states, the degree of agitation and gait, as well as training the CCR for empathy-based conversational interventions for aims 2 and 3. The second IRB request (human subject research in the minimal-risk biomedical track) was approved in March 2024 for all aims (UCI IRB #4150). The IRB approval includes access to medical records and the observation of clinical care, and a partial waiver of Health Insurance Portability and Accountability Act (HIPAA) authorization has been requested.

#### Informed Consent

##### Family Caregivers and Health Care Professionals

At the beginning of the study, a study team member will provide family and professional caregivers with comprehensive information about the study and obtain their consent.

##### Participants With Dementia

As the participants with dementia might be cognitively impaired, the informed consent procedure will use a validated decision-making assessment tool [33] tailored to the cognitive abilities of participants with moderate to severe dementia. This tool will assess each participant’s capacity to comprehend the study objectives and procedure and determine their capability to provide informed consent regarding participation in the study. If the assessment indicates the participant’s lack of decision-making capacity to provide informed consent independently, a surrogate decision maker who is a legally authorized representative or a family member will be identified. The study team will inform the decision maker about the study, provide comprehensive details, and obtain their consent on behalf of the participant.

In addition, despite requiring surrogate consent, efforts will be made to obtain assent from the participant whenever possible. The assent process involves presenting information about the study in a manner that aligns with the participants’ cognitive abilities; seeking their agreement or disagreement (through words or nonverbal cues, including body language, facial expressions, gestures, or signs of agitation or discomfort when study-related discussions arise); and respecting their preferences to the best extent feasible.

However, because the study involves individuals with moderate to severe dementia, we anticipate fluctuations in decision-making capacity due to the natural progression of the disease. Consequently, participants’ ability to provide or withdraw informed consent may vary throughout the study duration. Therefore, because regular assessments of decision-making capacity are essential, qualified professionals will continue to evaluate participants’ ability to comprehend study information and make informed decisions. If, during the study, individuals demonstrate a diminished capacity to provide consent, the protocol outlines procedures for involving surrogate decision makers or legally authorized representatives to act in the participant’s best interests. It is essential to mention that participation in the study is completely voluntary, and all participants can opt out at any time without consequences.

#### Privacy and Confidentiality

The participants’ personal information and identifiers will be kept separate from the study data, and a code will be assigned to each participant. The deidentified data will be used for analysis and training purposes. After capturing audio and visual data of participants for whom they or their family members or legal guardians have provided consent, we will use the ARX data anonymization tool to anonymize sensitive personal data. All geographic locations, contexts, and environmental data will be abstracted to ensure that the collected data cannot be traced back to their original providers and will not be transmitted or stored in our cloud servers. In the cloud servers, the participants’ data will be processed using automated tools. We will make all relevant deidentified data and findings available after publication and will honor intellectual property rights.

The single electronic file containing participant identifiable information will be password protected and stored on a laboratory computer in the principal investigator’s locked laboratory, to which only the lead researcher, coresearchers, and study coordinators will have access. Research data will be stored electronically on a secure cloud-based data collection storage system maintained by the UCI Computer Science team led by a co-investigator.

As the audio recordings serve as primary training data for the CCR, it is crucial to preserve the integrity of identifiable audio recordings without transcription to preserve voice characteristics such as tone, intonation, and nuances in speech patterns, which are crucial for capturing the full complexity of human speech in developing ML algorithms. Therefore, the audio recordings will not be transcribed to prevent a loss or distortion of training data quality. However, deidentification procedures commence immediately after the audio recordings are obtained, ensuring minimal delay in protecting participant confidentiality.

The deidentification process for audio recordings involves several steps: (1) using specialized software such as Audacity or Adobe Audition designed for deidentification purposes; (2) using voice masking methods (including pitch shifting, time stretching, or applying filters to modify the frequency characteristics of the voice) within these tools to alter the pitch, tone, or timbre of the participants’ voices to make them less recognizable; (3) conducting quality checks to ensure that all identifiable information has been effectively removed or altered; (4) using speech intelligibility metrics such as signal-to-noise ratio, mean opinion score, and perceptual evaluation of speech quality to objectively measure the clarity of the modified audio; and (5) finally storing the deidentified audio recordings securely in a protected database to prevent unauthorized access. Similarly, preserving identifiable video recordings without transcription is crucial for comprehensive emotion and agitation detection as well as gait analysis, especially in training the CCR. These recordings contain critical contextual cues, facial expressions, body language, and environmental elements, and deidentification risks the integrity of developing precise training models. Therefore, the video recordings will not be deidentified.

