###### Modeling Emotional States

To model the emotional state of a person experiencing moderate to severe dementia, we will design multimodal ML and AI models using 4 types of data: natural language content, facial expression, body movements, and vocal features. We will focus on modeling emotions from each modality (eg, text as natural language content) and then integrate these models to create a comprehensive multimodal model. The goal is to evaluate the emotional content of a conversation at a particular point in time. In establishing these models, we consider both theoretical and technical aspects to ensure robustness. Specifically, in the case of the text modality, we will adapt existing theories (eg, the theory postulated by Parrott [37]) and ML and AI techniques (eg, pretrained models, such as Robustly Optimized Bidirectional Encoder Representations From Transformers Pretraining Approach [RoBERTa] [38], with fine-tuning) for inferring emotions from natural language to the context of dementia when modeling emotions using text extracted via speech-to-text techniques (for a comprehensive review, refer to the study by Zad et al [39]). This is especially pertinent to feature representation processes. In these processes, we will obtain word embeddings for emotions with the assumption that multiple emotional states can coexist simultaneously (for further information, refer to the study by MohammadiBaghmolaei and Ahmadi [40]). Our analysis will focus on 6 distinct emotional states: sadness, fear, joy, love, surprise, and anger. In the modeling process, we will pretrain our models on open-source data sets widely used for emotion recognition tasks in the natural language processing community (eg, the Interactive Emotional Dyadic Motion Capture Database [IEMOCAP] [41]) and then retrain them on data sets focused on conversation data from persons experiencing moderate to severe dementia, using both open-source data sets (eg, DementiaBank [42]) and our own (ie, the National Institute on Aging [43]).

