Beyond the text modality, we will also train a deep learning model, using images and videos containing the facial expressions of a person experiencing moderate to severe dementia to infer emotions such as joy, sadness, or anger from their smiles, frowns, brow movements, and lip configuration. We will train our models using large image data sets such as Facial Expression Recognition 2013 [44], while also considering retraining them on data sets specific to patients with dementia [45,46]. In addition, videos and motion sensors will be used to infer emotions from a patient’s body movements. Audio data will be used to infer emotions based on markers such as speech rhythm, voice intensity, and other spectral features (eg, mel-frequency cepstral coefficients). Empathy modeling, including the alignment of LLMs using prompt engineering and reinforcement learning techniques, will also be conducted, considering the relationship between emotion and empathy.

Our research aims to make scientific contributions to ML and AI for emotional intelligence and empathetic conversation of CCRs in two main ways: (1) designing a new multimodal model for empathy classification that enables CCRs to sense a patient’s emotional state in real time; and (2) aligning LLMs for empathy using various techniques, such as prompt engineering, reinforcement learning, or a combination of both. For the first point, we plan to build a semisupervised ML model that uses a transformer architecture and pretrain it on healthy data sets. We will evaluate this baseline using dementia data sets carefully labeled by domain experts with respect to the emotional state of patients with dementia. We will then improve this baseline model by enhancing its self-supervision based on features identified from 4 modalities (ie, natural language content, facial expressions, body movements, and vocal features) in data collected from patients with dementia. We will examine different ML and AI models and evaluate their performance in both quantitative and qualitative ways.

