Concurrently, a team from NaviGAIT and computer scientists from UCI are working on detecting agitation. We used the collected data and trained several models to detect different types of motions, such as sitting, standing, and so on, and annotate the video every 3 seconds. Currently, we are at the phase of training the model and improving its accuracy in detecting agitation. For audio, we are able to detect audio events using the Agitation Maker, which converts the audio into text and applies semantic scoring using a generative pretrained language model to obtain an agitation score. This work is under progress.

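### Residents' audio is to keep its tone and intonation for training, yet it is voice-masked on capture and barred from transcription, which conflicts with the planned voice and text models

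*Protocol article*

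**What the plan says.** Under Ethical Considerations, Privacy and Confidentiality, the protocol article makes these statements about residents' audio:

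- It is primary training data for the robot, and its tone, intonation and speech-pattern detail must be kept.
- For that reason "the audio recordings will not be transcribed to prevent a loss or distortion of training data quality".
- Nevertheless "deidentification procedures commence immediately after the audio recordings are obtained".
- Deidentification means "using voice masking methods (including pitch shifting, time stretching, or applying filters to modify the frequency characteristics of the voice", with the stated aim "to alter the pitch, tone, or timbre of the" participants' voices.
- On what feeds the models: "The deidentified data will be used for analysis and training purposes".
- After masking, the checks are that identifiers are gone and that the modified audio is clear (signal-to-noise ratio, opinion score, perceptual quality).
- Video is exempt from deidentification, because deidentifying it would put the training models at risk.

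The modelling sections state what the models need from audio:

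- Modeling Emotional States: "Audio data will be used to infer emotions based on markers such as speech rhythm, voice intensity, and other spectral features", and the text modality is built "when modeling emotions using text extracted via speech-to-text techniques".
- Plan for Pretraining the Robot: pitch, energy and mel-frequency cepstral coefficients are extracted.
- Results, Activity 2: the audio agitation tool "converts the audio into text and applies semantic scoring".

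**The concern.** The privacy section both requires tone to be preserved and requires it to be altered, and it says that the altered version is used for training. It recognises this harm for video and exempts video, but gives audio no such exemption.

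The stakes come from where the models are used. They decide when the robot approaches a resident (Pilot Implementation), and they also supply the Aim 4 measurements of emotional state and agitation (Evaluation, Quantitative). If the voice component is trained on masked resident speech and then applied to live speech, training and use differ systematically, and both the trigger and the outcome measure receive that input.

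The planned laboratory check might not reveal the problem. Simulated Validation plays residents' recordings to the robot without saying whether these are the masked versions.

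The transcription sentence raises a separate difficulty. Taken literally, it removes the source of resident text for the language modality and the agitation score. It would also affect the story graph, which draws on residents' recorded conversations (Collecting Personal Stories).

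**Working it through.** The documents give no figure to reproduce: there is no masking strength and no error rate for masked speech. The check sets the handling rules beside the model inputs.

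**Step 1. Does the privacy section agree with itself?** It says to keep tone and intonation, to alter pitch, tone or timbre immediately, and to train on the altered version. These cannot all hold for one copy of a recording, and the section names no second copy for training.

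**Step 2. Does masking alter what the models extract?** The methods are listed with *or*, so each is taken alone.

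| Masking option | Feature necessarily changed | Where that feature is needed |
|---|---|---|
| Pitch shifting | Pitch | Plan for Pretraining the Robot |
| Time stretching | Speech rhythm | Modeling Emotional States |
| Frequency filtering | Spectral coefficients | Both of those sections |

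No option leaves every required feature intact.

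**Step 3. Would the stated checks detect the loss?** No. They test removal of identifiers and clarity. Speech can be clear while its pitch or rhythm has changed.

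**Step 4. Is speech-to-text allowed?** The no-transcription sentence has no exception. Modeling Emotional States and Results, Activity 2, both depend on converting audio to text.

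**Step 5. How far does it reach?** Modeling Emotional States lists four modalities: language, face, movement and voice. Language and voice come from audio, so 2 of 4 are touched, voice by masking and language by the transcription sentence. The masking rule covers the study's own recordings. The open sets (IEMOCAP, MELD, and DementiaBank with 78 patients) do not fall under it.

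**Step 6. Illustration with assumed settings.** These strengths are assumptions, not figures from the plan.

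- A pitch shift of s semitones multiplies fundamental frequency by 2^(s/12): s = 2 gives 1.12, s = 4 gives 1.26, s = 6 gives 1.41. That is a rise of 12% to 41%.
- Stretching duration by a factor k multiplies speech rate by 1/k: k = 0.8 gives 1.25, k = 1.2 gives 0.83.

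This shows that the named features move directly with the masking. It says nothing about how much classification error would follow.

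**The case against.** Much of the case on the other side stands, and it limits the point.

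- **Transcription.** The reason given for the ban is to avoid losing voice quality. That fits a rule against replacing audio with a transcript. Deriving text while keeping the audio loses nothing, and two sections plan exactly that. A reader might infer that the text model gets no resident data, but the documents do not establish this. What remains is that the sentence is unqualified and needs rewording.
- **Which audio is used.** The section also speaks of preserving identifiable recordings, so an unmasked training copy may be intended. The cameras record voice, and nothing says whether the video soundtrack is masked. Against this stands the explicit sentence that deidentified data are used for training.
- **Degree of damage.** A uniform pitch shift multiplies all pitch values alike, so relative intonation may survive. No recording need be both shifted and stretched. To call the voice modality corrupted would overstate the case.
- **Downstream effect.** A reader might infer that the robot's trigger and the Aim 4 scores will be miscalibrated. That is possible but not shown. The agitation model rests largely on images, video, motion sensors and remote photoplethysmography, with vocal data added (Modeling the Degree of Agitation). The plan also accepts some inaccuracy in identifying specific emotional states (Real-Time Sensing to Create Personicles).

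The open data sets soften the problem without removing it, since the residents' own recordings are described as primary training data.

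**Conclusion.** The contradiction is real and lies in what the article states, not in detail left to a fuller document. Followed as written, the voice model's resident data would be masked signals with at least one required feature altered, and no check would show whether emotional information survived. The robot would meanwhile listen to unmasked speech. The transcription sentence conflicts on its face with the planned speech-to-text.

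The reach is two of four emotion modalities, for the study's own recordings only. The effect on classification or on Aim 4 results cannot be sized, because no masking strength is given. The conclusion assumes that the sentence on training with deidentified data applies to audio and that live speech is not masked; nothing in the article says otherwise. It does not support saying that two modalities fail or that the Aim 4 outcomes are invalid.

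The passages should be reconciled before resident audio is processed. If originals are not kept, features lost to masking may not be recoverable.

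**What to change.** Change the order of processing and say which version feeds what.

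1. State that acoustic features (pitch, energy, rhythm, spectral coefficients and any learned speech representation) and automated speech-to-text are derived from unmasked audio before masking. Do this on the study workstation described in Results, Activity 1, which already receives recordings by a secure pipeline. Name these derived data as the training and analysis inputs, and amend the sentence on training with deidentified data to match.
2. Apply voice masking to copies stored in the cloud or shared.
3. Reword the transcription sentence: transcripts do not replace the audio, and local automated speech-to-text is allowed.
4. Keep names needed for the personal-story graph in the access-restricted local data, and redact them only in shared text. Redacting them everywhere would undercut the personalised storytelling.
5. State which audio version is played in Simulated Validation, and whether the video soundtrack is masked.

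**Cost.** An ethics-board wording amendment, an extraction step in the pipeline, and a short period of holding unmasked audio. That relaxes the present commitment to minimal delay, so the period should be stated. It would need to run longer if the feature set is revised during model development. The added exposure is comparable to that of the unmasked video already retained.

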#### Compensation

For aims 1 and 4, interviews will take place with family and professional caregivers, and a compensation of US $20 will be provided per interview. We anticipate conducting interviews with 8 to 14 family and professional caregivers for aim 1 and with 6 to 12 family and professional caregivers for aim 4. In addition, we will compensate approximately 50 students who will take part in the simulation laboratory role-plays (aim 3) with US $10 each.

### Research Description

#### Aim 1

For aim 1, we will collect and store granular Personicle data using real-time visual, audio, and physiological sensing technologies (including the CCR) to gain a deeper understanding of the emotional state, agitation level, and gait pattern of a person experiencing moderate to severe dementia over time.

##### Activity 1: Real-Time Data Collection and Sensing

The miles and outcomes involve creating (1) a database to store the hourly activities and behavioral states of a person experiencing moderate to severe dementia in real time and (2) a database to store their stories as episodic knowledge graphs.

###### Real-Time Sensing to Create Personicles

We will capture the behavioral states and patterns of a person experiencing moderate to severe dementia through real-time “lifelogging” using motion-sensing red-green-blue cameras with video capture and voice recording capacity (Microsoft Kinect), optical motion sensors (light detection and ranging [LIDAR] sensors), and remote photoplethysmography (rPPG) [34]. rPPG is a noninvasive optical technique used to estimate physiological parameters (eg, heart rate) remotely from a distance without the need for direct contact with the skin. The cameras and sensors will be installed in 2 bedrooms and the living room at 1 board and care facility at a time. We will begin observation of 2 patients at a time over at least a 2-month period, starting in month 2 and continuing until month 15, to capture the logs of 8 to 14 persons experiencing moderate to severe dementia. At least 6 to 8 persons experiencing moderate to severe dementia will remain for the full 2 years. In month 16, we will introduce the CCR and also use it as a real-time sensing device (using its onboard camera and LIDAR sensor). The CCR’s vision system is equipped with a human identification system. It can recognize >1 patient and track them (the CCR is also capable of identifying the caregivers). This allows the CCR to log the gait pattern, activities, and agitation level of the person under observation. This system will be configured during the start-up or onboarding process.

These sensing technologies will capture lower-level atomic, person-centric data—the “logs”—with a timescale of 1 minute that can be enriched with higher-level, more meaningful behavioral states using the models developed in activity 2. Specifically, we will model the emotional state, agitation level, and gait pattern of a person experiencing moderate to severe dementia and design a multimodel taxonomy and activity and states ontology, extending the existing Personicle, a person-centric temporal activity and states database developed at the UCI Institute for Future Health. For the purpose of recognizing agitation, our initial approach involves constructing models that leverage audiovisual sensing technologies. These models are designed to accurately recognize and categorize standard agitated behaviors as outlined in the Cohen-Mansfield Agitation Inventory [35,36]. This inventory includes a range of specific activities, such as kicking, grabbing, pushing, throwing objects, and screaming. After successfully capturing and classifying these activities, the next phase will focus on using these models to evaluate and quantify agitation levels in individuals with moderate to severe dementia. We will store activities or states at the minute level. This ontology will be used in activity 2 to find the relationships among the hourly or daily states and activities and to create a robust temporal activity model.

The ultimate goal of the CCR system is to develop a dynamic model that accurately captures an individual’s behavioral patterns. This model is intended to iteratively adapt and respond in a manner that positively influences and enhances these behaviors. In pursuit of this objective, a certain degree of tolerance for inaccuracy is considered acceptable, particularly in the precise identification of specific emotional states or the exact nature of agitated symptoms. This approach acknowledges that while exact details are beneficial, the primary focus is on the overall effectiveness of the model in improving behavioral outcomes.

